## Abstract

**Background:**

Acute lung injury (ALI) is an example of a critical care syndrome with limited treatment options once the condition is fully established. Despite improved understanding of pathophysiology of ALI, the clinical impact has been limited to improvements in supportive treatment. On the other hand, little has been done on the prevention of ALI. Olmsted County, MN, geographically isolated from other urban areas offers the opportunity to study clinical pathogenesis of ALI in a search for potential prevention targets.

**Methods/Design:**

In this population-based observational cohort study, the investigators identify patients at high risk of ALI using the prediction model applied within the first six hours of hospital admission. Using a validated system-wide electronic surveillance, Olmsted County patients at risk are followed until ALI, death or hospital discharge. Detailed in-hospital (second hit) exposures and meaningful short and long term outcomes (quality-adjusted survival) are compared between ALI cases and high risk controls matched by age, gender and probability of developing ALI. Time sensitive biospecimens are collected for collaborative research studies. Nested case control comparison of 500 patients who developed ALI with 500 matched controls will provide an adequate power to determine significant differences in common hospital exposures and outcomes between the two groups.

**Discussion:**

This population-based observational cohort study will identify patients at high risk early in the course of disease, the burden of ALI in the community, and the potential targets for future prevention trials.

## Background

Acute lung injury (ALI) and its more severe form Acute respiratory distress syndrome (ARDS) are common and devastating complications after acute illness or injury with high morbidity and mortality, long term decrease in quality of life, and enormous costs related to intensive care and rehabilitation [1]. ALI is an example of a critical care syndrome with limited treatment options once the condition is fully established. Despite improved understanding of the pathophysiology of ALI, the clinical impact has been limited to improvements in supportive treatment [2,3]. Surprisingly little research has been done on the prevention of ALI. Preclinical studies support a "two hit" model of development of ALI whereby different exposures modify the expression of ALI in susceptible host [4]. Preliminary data suggest that ALI is rarely present at the time of hospital admission but develops over a period of hours to days in subsets of patients with predisposing conditions such as pneumonia, sepsis, trauma, shock and corresponding medical and surgical interventions [5-12]. To this extent, ALI may be viewed as potentially preventable hospital complication similar to stress ulcer bleeding, venous thromboembolism or nosocomial infections. Previous clinical studies enrolled patients after ICU admission, often with already established ALI, beyond the window of meaningful mechanistic studies and potential prevention strategies [13-15]. Not surprisingly, many treatments targeting the mechanisms identified in preclinical studies have failed to improve patient outcomes despite compelling preclinical data [16-19]. It is likely that, inadequate and delayed recognition of patients at risk and the subsequent development of the full blown syndrome have obscured the therapeutic window. ALI usually develops during the first hours of ICU admission, and often is the very reason for ICU admission. On the other hand, the majority of patients with predisposing conditions never develop ALI and they may never been admitted to the ICU making the enrollment of unselected patients into ALI prevention studies neither feasible nor efficient [12,10]. A meaningful approach to ALI prevention therefore ought to be based on identifying patients at risk earlier than what is currently done (at the time of hospital admission, rather than ICU admission, Figure 1) [10].

**Figure 1 F1:**
[figure not shown]
**Proposed "two hit" model of ALI development: the window of opportunity exists for the potential ALI prevention strategies**.

## Methods/Design

In this population based cohort study the investigators will identify patients at risk early in the course of the disease and *before *the development of ALI (at the time of hospital admission). Detailed in-hospital exposures, short and long term outcomes will be compared between patients at high risk who do and do not develop ALI. (Figure 2)

**Figure 2 F2:**
[figure not shown]
**Outline of the study design**.

### Inclusion Criteria

Olmsted County residents more than 18 years of age admitted to the two Mayo Clinic Rochester hospitals with one or more of the ALI predisposing conditions (sepsis, pneumonia, aspiration, pancreatitis, shock, high risk trauma, and high risk surgery). (Table 1) Exclusion criteria are listed in Table 2. Institutional review board has approved the study protocol.

**Table 1 T1:** Predisposing conditions and modifiers available before or within six hours after hospital admission used to calculate the lung injury prediction score (LIPS):[22].

*Risk factors*	Measurement	Definition
Pneumonia	Yes/No	Consensus Conference[24]
Sepsis	Yes/No, severe	SCCM-ACCP definition[25]
Pancreatitis	Yes/No	Practice guidelines in acute pancreatitis[26]
Aspiration (pre-admission)	Yes/No	Inhalation of food or gastric contents[27]
High risk trauma	Lung contusion, smoke inhalation, near-drowning, multiple bone, brain injury	From Derdak [28]
High risk surgery	Aortic vascular, spine, thoracic, acute abdomen, emergency	From Arozullah et al [29,30]
*Risk Modifiers*		
Alcohol use	Yes/No, amount (# of drinks a week)	More than 2 drinks per day or a history of alcohol-related illness or admission[31,32]
Smoking	Never/former/current/# of pack-years	Substance Abuse and Mental Health
Diabetes mellitus*	Yes/No	Diabetes care 2009[33]
Interstitial lung disease	Yes/No	ATS-ERS Consensus classification of IIP[34]
Chemotherapy	Yes/No	Custom, cancer chemotherapeutic drugs during the 6 months prior to hospitalization
Tachypnea (respiratory rate>30),		Based on the worst value during the first 6 hours
High inspired oxygen concentration (FIO2>0.35)		Based on the worst value during the first 6 hours
Hypoalbuminemia		Serum albumin <3.5 g/dL, the absence of measurement considered normal

*Only if sepsis

**Table 2 T2:** Exclusion criteria.

Exclusion Criteria	Justification
Acute lung injury or pulmonary edema already present at the time of hospital admission	Unable to assess for development of outcome of interest
Admitted for comfort or hospice care only	Missing predictor and outcome variables
Denied the use of medical records for research (~5%)	Self explanatory
Patients admitted for cardiac telemetry, coronary care unit, low risk elective surgeries, labor and delivery	Very low risk of outcome of interest
Children	Different risk factors and outcome
Hospital readmission	Complexity of analysis
Hospital transfer	Exposure to health care interventions

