### Early identification of patients at risk of ALI (lung injury prediction score - LIPS)

To facilitate enrollment of patients into mechanistic and outcome studies as well as future ALI prevention trials, we have recently developed an ALI prediction model (Lung Injury Prediction Score: LIPS, Table 1)[22]. LIPS incorporates demographic, and clinical characteristics at the time of, and before, hospital admission. Risk factors for ALI that were identified in at least two previous studies were used in model development. LIPS points were determined based on parameter estimates from the logistic regression model, taking into consideration results from our previous studies. The model accurately discriminated between the patients who did and did not develop ALI with an area under the receiver operating curve of 0.85 (95% CI 0.80 to 0.89) [22].

Twice daily (7 AM and 5 PM, Monday-Saturday) trained study coordinators review syndrome surveillance alerts of new Olmsted County admissions and apply LIPS points to patients who fulfill the inclusion criteria according to LIPS score sheet. ODBC MS Access database tool is used for the collection of individual patient data in a systematic way. The database automatically links MS Access to ICU Datamart server and imports new patients from ICU Datamart to the LIPS database. The database also links automatically to the IRB research authorization web site identifying the patients that have approved the use of their medical data for research.

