### Validation of the primary outcome (ALI)

Primary outcome is the development of ALI at any time during the hospital stay. Trained investigators review each ARDS sniffer alert (see above) and confirm the presence or absence of ALI according to the standard definition based on the American-European consensus conference [21]. The absence of left atrial hypertension as the principal explanation for pulmonary edema is confirmed by integrated clinical evaluation based on the following:

• Echocardiography (E/E'<15, EF>45)

• Pulmonary artery occlusion pressure (PAOP) ≤ 18 cm H2O

• Central venous pressure (CVP < 15) cm H2O (higher cutoff in pulmonary hypertension)

• History of congestive heart failure/cardiogenic pulmonary edema

• Brain natriuretic peptide (BNP) <250 pg/mL (higher cutoff in renal failure)

• Response to preload reduction: brisk (hours) response to diuretics and/or positive pressure ventilation favors hydrostatic edema

This process yielded good interobserver agreement for differentiation between ALI and hydrostatic edema (Kappa value 0.83 in the most recent retrospective Olmsted county study)[10].

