### Identification of in-hospital exposures

To identify candidate interventions for ALI prevention, we are planning to identify hospital acquired (2^nd ^hit) environmental exposures that may modify the risk of ALI and its consequences in high risk subgroups of patients residing in the Olmsted County community identified by the LIPS model. Timing and intensity of environmental exposures (Table 3) will be determined by the review of monitoring logs, nursing and physician interventions in the EMR by trained study coordinators blinded to ALI status. Only the exposures occurring before development of the ALI in cases and during the corresponding period of time in controls will be analyzed as modifiers of ALI development.

**Table 3 T3:** Hospital (second hit) exposures that may modify the development of ALI in high risk patients.

	Variable	Measurements

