### Statistical Analysis

An estimate for the probability of ALI development will be calculated for each patient based on the LIPS model. Because of subjective nature of clinical definitions used to identify the outcome of our study, it is necessary to assess interobserver variability. Interobserver agreement for ALI development will be assessed by calculating the Kappa statistic, using a threshold of 0.6 as an indication of acceptable interobserver agreement.

The calibration and discrimination of model will be assessed using the Hosmer-Lemeshow goodness-of-fit test and the receiver operating characteristic curve, respectively. An area under the ROC curve greater than 80% will be considered to be the evidence of good model discrimination. Using a LIPS cutpoint of 3.5 or more identified in the preliminary data, the comparison of the model prediction versus the actual event observed will be summarized by a simple 2 by 2 table reporting ALI propensity versus ALI development. Summary measures, based on the 2 by 2 table, will be reported: sensitivity, specificity, positive predictive value, negative predictive value, positive and negative likelihood ratios along with their 95% confidence intervals.

In a matched case-control design the associations suggested by preliminary clinical studies (Table 3) will be compared between ALI cases and high risk controls propensity matched by age, gender and the probability of ALI development at the time of hospital admission (LIPS, see above). Subpopulation analyses will be performed to determine what hospital exposures are associated with ALI in low/moderate ALI risk patients and what hospital exposures factors are associated with no ALI development in high ALI risk patients. The primary statistical endpoint is the development of ALI at any time during hospital stay. The matching is based on ALI risk at admission and the exposure period at risk. For example, if a hospitalized patient, who has an estimated propensity for developing ALI of 20% actually develops ALI 10 hours after hospital admission the exposures in matched control patient is only measured during the initial 10 hours after hospital admission. Paired statistics will be used for group comparisons. A conditional logistic regression model will be built in the case of baseline imbalances.

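### LIPS reads the worst FIO2 and respiratory rate over hours 0-6 with no cut-off at ALI onset, so early ALI can feed its own predictor, and early FIO2 is both a matching input and a tested exposure

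*Protocol article*

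**What the plan says.** **Score window.** The title of Table 1 (Inclusion Criteria) covers "Predisposing conditions and modifiers available before or within six hours after hospital admission used to calculate the lung injury prediction score". Tachypnea (rate above 30) and "High inspired oxygen concentration (FIO2>0.35") are each scored "Based on the worst value during the first 6 hours". Nothing says that readings stop counting once ALI has begun.

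**Outcome window.** Table 2 excludes "Acute lung injury or pulmonary edema already present at the time of hospital admission". Under Validation of the primary outcome, "Primary outcome is the development of ALI at any time during the hospital stay". ALI at hour 1, 3 or 5 is therefore a counted case.

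**Exposure window.** Under Identification of in-hospital exposures, the analysis takes "Only the exposures occurring before development of the ALI in cases and during the corresponding period of time in controls". The worked example in Statistical Analysis (a case with onset at 10 hours) starts the clock at admission: "the exposures in matched control patient is only measured during the initial 10 hours after hospital admission".

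**Matching.** Statistical Analysis matches controls on age, gender and the LIPS probability, which it describes as risk at admission. Part A of Table 3 lists FIO2 and respiratory rate as exposures under respiratory support, each summarised by area under the curve, mean, median and maximum.

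**Timing in the text.** The section on early identification says "LIPS incorporates demographic, and clinical characteristics at the time of, and before, hospital admission". Table 1 and the Abstract both use a six-hour window instead.

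**The concern.** Two problems follow from applying these windows together.

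1. **Validation.** For a patient whose ALI begins inside the first six hours, the worst FIO2 and respiratory rate may be readings taken after onset. ALI screening is triggered by PaO2/FIO2 below 300, so the hypoxaemia that marks the outcome can also raise the FIO2 item. A predictor recorded after the event then helps to predict it. The ROC area, the 2 by 2 table at the 3.5 cutpoint and the calibration test all rest on that score.

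2. **Matched comparison.** The maximum FIO2 in hours 0-6 is the quantity behind the LIPS item and is also part of the Table 3 exposure. Pairing on a score that contains it removes part of the contrast to be estimated. Conditional logistic regression, planned for baseline imbalances, cannot restore a contrast that the matching has removed.

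At stake are the claim that LIPS identifies risk before ALI develops and the credibility of FIO2 as a prevention target.

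**Working it through.** The plan gives no figure for this point. The main check sets the windows side by side; the arithmetic is illustrative.

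**Step 1: windows**

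| Quantity | Starts | Stops |
|---|---|---|
| LIPS FIO2 and respiratory rate | admission | hour 6, whether or not ALI has begun |
| ALI as outcome | after admission | end of stay |
| Table 3 exposures | admission | ALI onset, or the same hour in the control |

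Exposures are cut at onset and LIPS inputs are not. Aspiration is split into pre-admission (Table 1) and in-hospital (Table 3); FIO2 and respiratory rate are not split. No landmark or lag is stated.

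**Step 2: share of the exposure window inside the scoring window**

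Share = min(6, T)/T for onset at hour T:
- T of 6 or less: 100%
- T = 10, the plan's example: 6/10 = 60%
- T = 48: 6/48 = 12.5%

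**Step 3: possible inflation of the ROC area**

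Assumptions, none from the documents: a share f of cases is early; 70% of those gain s standard deviations of score from post-onset values; scores are normal with equal variance. With true area A0 and d = √2·Φ⁻¹(A0), the area for the raised cases is A1 = Φ((d + s)/√2), and the apparent area is (1 − 0.7f)·A0 + 0.7f·A1.

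For A0 = 0.85 (the protocol's estimate, 95% CI 0.80 to 0.89), d = 1.466:
- s = 1.5: A1 = Φ(2.097) = 0.982. f = 0.1, 0.2, 0.3 gives 0.859, 0.869, 0.878.
- s = 0.5: A1 = Φ(1.390) = 0.918. The same f gives 0.855, 0.859, 0.864.

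For A0 = 0.79, d = 1.140, and s = 1.5: A1 = Φ(1.867) = 0.969, giving 0.803, 0.815, 0.828.

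The increase is therefore about 0.005 to 0.04 over these inputs.

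**Step 4: what matching on the score does to early FIO2**

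Let E be high FIO2 in hours 0-6, B the rest of the score, and logit P(ALI) = α + βB + θE. The score is L = B + wE, where w is the points for the item. Substituting B = L − wE gives

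logit P = α + βL + (θ − βw)E.

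Pairs matched exactly on L thus estimate exp(θ − βw), not exp(θ). With assumed β = 0.45 and a true odds ratio of 2:
- w = 1: 2/e^0.45 = 2/1.568 = 1.28
- w = 2: 2/e^0.90 = 2/2.460 = 0.81

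A simulation of 1:1 matching with these inputs and no early ALI gave 1.25 and 0.87. Matching on the score without the item returned 1.9 to 2.1. When 10% to 50% of cases were early and their scores took in post-onset FIO2, the estimates fell to 1.18-1.08 (1 point) and 0.69-0.51 (2 points).

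If the points equal the item's own log odds ratio (βw = θ), the matched odds ratio is 1. The protocol says that the points were based on logistic regression estimates, so a result near 1 for the dichotomised early item would be no surprise, whatever its true effect.

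**The case against.** **The size is not known.** This stands. The Background says only that ALI develops over hours to days. The share within six hours, the item points and the onset times are not given. The supportable statement is that LIPS can be contaminated, not that it is.

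**A reader might infer that the inflation carries LIPS over the plan's 0.80 criterion.** The documents do not support that. In Step 3 the crossing occurs only from a start just below the threshold. From the 0.85 that the protocol reports, the pass or fail conclusion is unchanged. Whether that 0.85 used the same six-hour window is not stated.

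**A reader might infer that the matched estimate is always pulled toward the null.** Step 4 shows otherwise: depending on the points, it can be attenuated, null or reversed.

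**Respiratory rate may not be the same variable.** This is fair. In Table 3 it sits with tidal volume, airway pressures and PEEP and may be a ventilator setting, whereas Table 1 scores a patient sign. FIO2 is the clear overlap. Even there, LIPS uses one cut at 0.35, while Table 3 also uses area, mean and median, so the loss is partial.

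**Early FIO2 marks severity and ought to be matched on.** Also fair. The Discussion names indication bias as a limitation, so matching on a LIPS stripped of these items would reopen severity confounding for exactly these exposures. But if hours 0-6 serve as severity, the same hours cannot also be the tested exposure.

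**The timing conflict is loose wording.** Largely so, since the Abstract and the title of Table 1 agree on six hours. It still needs correcting, because it hides the overlap.

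**Conclusion.** The point holds in a limited form. As written, the rules let post-onset values into the score for ALI arising in hours 0-6, and they make early FIO2 both a matching input and a tested exposure. Respiratory rate joins it only if the Table 3 item means the patient's rate. Both follow from windows that the protocol itself fixes, not from detail left to another document.

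The effect on discrimination runs upward, but its amount cannot be derived from the documents. About 0.005 to 0.04 in ROC area is what the assumed inputs give. The effect on the matched FIO2 odds ratio is partial removal with distortion of uncertain direction. The 1.25 and 0.87 obtained from a true 2 are upper-end illustrations: they assume exact matching and an exposure lying wholly in hours 0-6. Exposures unrelated to the two items are not matched away. The change should be made; it does not invalidate the design.

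**What to change.** 1. **Scoring and validation.** State that LIPS inputs stop at ALI onset. Report the ROC area, the 2 by 2 table and calibration for ALI arising after hour 6 among patients ALI-free at hour 6. Report ALI in hours 0-6 separately with the truncated inputs, since a shorter reading window makes those scores not directly comparable with the rest.
2. **FIO2 as an exposure.** Start its window at hour 6 and use pairs whose case arises after hour 6. Earlier values then act as matched severity and later values as exposure. State whether the Table 3 respiratory rate is the patient's rate or a ventilator setting; if the former, treat it the same way.
3. **Wording.** Align the LIPS description in the early identification section, and the description of the matching variable in Statistical Analysis, with the six-hour window of Table 1.

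**Cost.** The work is re-analysis of data from the electronic record, with no new collection. Cases arising within six hours leave these analyses, so fewer than 500 support the precision statement in Sample size considerations. If 10%, 20% or 30% leave, a confidence half-width for sensitivity grows by 1/√0.9 = 1.05, 1/√0.8 = 1.12 or 1/√0.7 = 1.20. The validation endpoint becomes ALI after hour 6 rather than at any time, and the ROC area may be slightly lower.

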### System-wide electronic surveillance

Electronic medical records (EMR) facilitate early recognition of specific study criteria using Boolean combinations of clinical variables and natural language processing. In this study we are planning to use a customized, integrative relational research database that contains a near-real time (15 minutes delay) copy of electronic medical records (ICU DataMart). To identify Olmsted County residents at risk admitted to the two Mayo Clinic hospitals, ICU DataMart uses 9-digit ZIP code and a specific nursing unit codes and generates e-mail and/or pager alert within 15 minutes from the time the patient is assigned a bed in the receiving unit. Patients admitted for labor and delivery, specific procedures (cardiac catheterization), cardiac telemetry, coronary care unit, low risk elective surgeries and children are excluded from the alerts. Screening for ALI development is performed by previously validated ARDS "sniffer" [20,21]. The electronic alert is triggered by the following combination of observations: 1) qualifying arterial blood gas analysis: the ratio of partial pressure of oxygen to inspired oxygen concentration (PaO_2_/FIO_2_) <300 and 2) qualifying chest radiograph report: free text Boolean query containing trigger words: ("bilateral" AND "infiltrate") OR "edema" The ARDS sniffer demonstrated excellent negative predictive value (0.99, 95% CI 0.98 to 1.00)[20]. ARDS-sniffer has been continuously running since December of 2005 allowing for prospective identification of ALI cases. Access to the database is accomplished through password protected open database connectivity (ODBC) using JMP and SAS statistical software (SAS Institute Inc., Cary, NC, USA).

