The principal limitation of our study is imposed by the broad nature and definition of the primary outcome of interest, ALI [21]. The exclusion of left atrial hypertension poses a particular challenge in the clinical assessment of ALI. In addition to using a standardized definition and extensive training of study personnel, all ALI cases will be reviewed by trained expert investigators. There is a possibility of ascertainment bias as we will depend on the clinicians caring for the patient to order the chest x-ray and the arterial blood gas necessary to diagnose ALI. Fortunately, almost all patients requiring respiratory support do have these tests performed routinely every day. It is therefore extremely unlikely that a significant ALI would occur without the need to perform the chest x-ray and the arterial blood gas as a part of clinical care.

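### Patients moved to comfort care after admission have no stated outcome or control-eligibility rule and, if untested, count as ALI-negative by default

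*Protocol article*

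**What the plan says.** - **Eligibility.** Table 2 (Inclusion Criteria) excludes patients "Admitted for comfort or hospice care only", with the justification "Missing predictor and outcome variables". The criterion applies at admission.
- **Follow-up.** The Abstract (Methods/Design) states that "Olmsted County patients at risk are followed until ALI, death or hospital discharge". A change in the goals of care is not among the end points of follow-up.
- **Outcome.** Validation of the primary outcome (ALI) states: "Primary outcome is the development of ALI at any time during the hospital stay".
- **How ALI is found.** Under System-wide electronic surveillance, an alert requires both a "qualifying arterial blood gas analysis" and a "qualifying chest radiograph report: free text Boolean query containing trigger words". The validation section then says: "Trained investigators review each ARDS sniffer alert (see above) and confirm the presence or absence of ALI".
- **Declared limitation.** The Discussion concedes that "we will depend on the clinicians caring for the patient to order the chest x-ray and the arterial blood gas necessary to diagnose ALI". It answers that patients on respiratory support have these tests daily, so a significant ALI is very unlikely to be missed.
- **Use of the outcome.** Statistical Analysis compares the lung injury prediction score (LIPS, cutpoint 3.5) with observed ALI over the stay in a 2 by 2 table. Controls are matched on risk at admission and on the period at risk, with their exposures cut at the matched case's onset time.

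**The concern.** By its own justification in Table 2, the plan treats the outcome as unobservable under comfort care. Once an enrolled patient's care becomes comfort only, the same doubt applies to the rest of that patient's stay. The stated rules nevertheless keep the patient in follow-up. If no blood gas and radiograph are taken there is no alert, and without an alert there is no route to any status other than ALI-negative. The missing-data methods in Statistical Analysis would not necessarily catch this, because an absent alert need not appear as a missing value.

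Two analyses are exposed:

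- **The LIPS 2 by 2 table**, which uses the whole stay. An unknown outcome in a patient at or above the cutpoint is counted as a false positive.
- **The matched comparison**, but only where care was limited before the matched case's onset. For example, a patient moved to comfort care on day 2 could be matched to a case with onset on day 3. That patient was not observably at risk for the whole window, which conflicts with the plan's own principle of matching on the period at risk.

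**Working it through.** **1. The rules side by side.** Exclusion for comfort care operates at admission only. Follow-up ends at ALI, death or discharge. Adjudication is driven by alerts, and an alert needs two clinician-ordered tests. Together these give an untested patient a default status of no ALI. The Discussion's reassurance concerns patients on respiratory support and does not address patients whose care has been limited. The alert's negative predictive value of 0.99 does not settle the matter, because the article does not describe care-limited patients in that validation.

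**2. The plan's own figure.** The Figure 3 caption gives about 82% power for 500 pairs, 5% of controls exposed and a 2-fold effect. Reading this as two proportions, p0 = 0.05 and p1 = 0.10, with two-sided alpha 0.05 and continuity correction:

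- Effective n = (500 − 1/0.05)²/500 = 480²/500 = 460.8 per group.
- z = [√(460.8 × 0.05²) − 1.96 × √(2 × 0.075 × 0.925)] / √(0.05 × 0.95 + 0.10 × 0.90) = (1.0733 − 0.7301)/0.3708 = 0.926.
- Power = 82.3%.

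The figure reproduces, so no stated number is wrong on this point.

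**3. Illustration for the 2 by 2 table.** From Sample size considerations: 500 cases and 80% sensitivity. Assumed, not in the documents: 10% ALI incidence, 80% specificity, and 5-10% of false positives switching to comfort care untested.

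- Cohort 500/0.10 = 5,000, so 4,500 without ALI.
- True positives 0.80 × 500 = 400; false positives 0.20 × 4,500 = 900; true negatives 3,600.
- Positive predictive value (PPV) as planned: 400/1,300 = 30.8%.
- Setting aside 45 unknowns (5%): 400/1,255 = 31.9%. Setting aside 90 (10%): 400/1,210 = 33.1%.
- Specificity: 3,600/4,455 = 80.8% and 3,600/4,410 = 81.6%, against 80.0% as planned.

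**4. Bounds on the same assumptions.** Counting none of the unknowns as ALI returns the planned table. Counting all of them as ALI gives:

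| Unknowns | PPV | Sensitivity | Specificity |
|---|---|---|---|
| 0 (as planned) | 30.8% | 80.0% | 80.0% |
| 45 | 445/1,300 = 34.2% | 445/545 = 81.7% | 80.8% |
| 90 | 490/1,300 = 37.7% | 490/590 = 83.1% | 81.6% |

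Only patients at or above the cutpoint are varied here. Switchers below it would become false negatives in the all-ALI bound and lower sensitivity.

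**5. A second set of assumptions, by share of true ALI unseen (u).** Assume sensitivity 0.80, specificity 0.75, ALI frequency 7%, and missing ALI independent of score. Then PPV = 0.80 × 0.07 × (1 − u)/(0.80 × 0.07 + 0.25 × 0.93) = 0.056(1 − u)/0.2885. For u = 0, 5%, 10% and 20% this gives 0.194, 0.184, 0.175 and 0.155. Observed specificity moves only from 0.750 to 0.748, 0.746 and 0.742. With ALI frequency 3% or 15% and u = 10%, PPV falls from 0.090 to 0.081 or from 0.361 to 0.325.

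**6. The matched comparison.** Suppose a share m of controls had unseen ALI before the matched onset, with the cases' exposure rate of 10%. Control exposure becomes 0.05(1 − m) + 0.10m. By the method of step 2:

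| m | Odds ratio | Power |
|---|---|---|
| 0 | 2.11 | 82.3% |
| 1% | 2.09 | 81.4% |
| 2% | 2.07 | 80.4% |
| 5% | 2.01 | 77.5% |
| 10% | 1.91 | 72.1% |

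This covers unseen ALI only. The article does not say how exposures change once care is limited, so the direction of that further effect cannot be determined.

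**The case against.** The strongest reply is that Table 2 lists entry criteria, and that coding a later change in the goals of care is a detail a condensed article may leave to the full protocol or analysis plan. The dependence on clinician-ordered tests is also disclosed as possible ascertainment bias. Both points have weight: the full document may hold a rule, and the general limitation is acknowledged. The concern is nevertheless with how rules that are stated combine, and the disclosed defence does not cover this group.

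Several further objections stand and limit the point:

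- Table 2 cites missing predictors as well as missing outcome. LIPS uses data from before or within six hours of admission, so a patient who switches on day 2 has complete predictors. Only the later outcome is in doubt.
- The article does not say that testing stops after a switch, how often switches occur, or in so many words that these patients are scored negative.
- Only a patient with true but unseen ALI is misclassified.
- A control who switches after the matched onset was under ordinary surveillance throughout the compared window and is valid.

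A reader might also infer that such patients inflate control mortality and so shrink the burden attributed to ALI. Twenty-five of 500 controls would be 5 percentage points. The planned hazard ratio of 1.25 on a two-year median implies, under exponential survival, six-month mortality of 1 − 0.5^0.25 = 15.9% against 1 − 0.5^0.3125 = 19.5%. The documents do not support the inference. Those deaths are real and need no blood gas to be recorded, the planned median is for the control population as a whole, and cases may have care limited too. Dropping such patients from the controls alone would itself exaggerate the effect of ALI.

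**Conclusion.** The point holds in limited form. The stated rules leave an enrolled patient who moves to comfort care and is not tested as ALI-negative by default, and nothing bars that patient from serving as a control for a later case onset. Some entries in the 2 by 2 table may therefore be wrong, and some controls may not be observably at risk for the full window. It would go too far to read this as showing that all such patients are misclassified, that the stated power is wrong, or that the survival comparison is biased.

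The size cannot be derived from the documents. On the assumed 10% incidence, 80% specificity and 5-10% switching among false positives, PPV moves by 1.1 to 2.3 points when the unknowns are set aside, and specificity by 0.8 to 1.6 points. These are illustrations, not corrected estimates. The change is worth making because it is cheap and follows from the plan's own matching principle.

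**What to change.** - Record the date and time of the first comfort-care-only order for every enrolled patient.
- Allow such a patient to serve as a control only for case onset times before that order.
- Keep the planned 2 by 2 table as the primary accuracy analysis. Beside it, show patients with no ALI before the order as a separate category. In a sensitivity analysis, report sensitivity, specificity, predictive values and likelihood ratios as bounds, with all of these patients counted as ALI and with none.
- Do not remove these patients from the control arm only. Any survival sensitivity analysis that involves limitation of care must apply the same rule to cases and controls.
- If the full protocol already contains such a rule, state it in the outcome and matching sections.

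The cost is one date field, taken from a record that the coordinators already review for exposures, plus a matching rule. The downside is a slightly smaller control pool and a wider range around the accuracy figures.
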